#### The number of participants projected at each site

The number of families to be recruited at each site was calculated based on the number of therapists trained at each site, with the expectation that each MATCH therapist would contribute with at least six cases each to the study, matched by an equal number of cases from TAU therapists. Six clinics participate at the present. Originally, one more outpatient clinic was recruited to take part in this trial. In the fall of 2016, however, it became clear that this clinic was not able to fulfill the requirements of participation and was, therefore, excluded from the trial, from therapist consultation, from the use of the PATH system, and all other MATCH elements. This decision was reached in agreement with the management at the clinic in question. We had originally planned to recruit 36 families from this site. Thus, the remaining six clinics have been asked to recruit, between them, the remaining families to compensate for the loss. As of fall 2017, we are in the process of recruiting two or three more clinics.

#### The selection of participants to be included in the analyses

We will answer two important research questions: First, to answer the question of “Does MATCH work?” we will employ a per-protocol design; thus only those children and families who have gone through treatment will be included. Second, the question of whether “MATCH makes a difference in existing clinics” is best approached via an intention-to-treat design (ITT), in which all families randomized will be included in the analyses, regardless of whether they entered or completed treatment. Thus, we will analyze data using both ITT and per-protocol designs in an effort to answer these two overall questions.

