### Procedures

#### Intervention/Route of administration

When the child and family have been randomized to a MATCH therapist, the therapist will also be informed regarding the child’s primary protocol. The therapist will bring the case to the consultation group led by a US consultant and receive consultation on how to start the treatment. The therapist will arrange with the family when to meet and the treatment will then be delivered at the clinic. The assigned primary protocol (either anxiety, trauma, depression, and/or conduct) will lead the sequence of modules used. A treatment will always involve more than one module. To manage clinical interference that requires deviation from the primary protocol, the therapist, in agreement with the consultant, can choose among several of the 35 modules. If there are any remaining difficulties that need to be addressed after the primary protocol has been completed, the therapist can start a new protocol.

Children and families in the comparison group, who receive TAU, are offered the treatment normally delivered in the clinic. The content and structure of TAU vary among clinics and among individual therapists. TAU therapists may deliver family-based therapy based on an eclectic approach; they may offer a standard, single-syndrome EBT (for example, Coping Cat or Parent Management Training) or enroll the child or family in group therapy. Families in both conditions complete PATH, but only MATCH therapists will have access to the families’ responses. Therapy sessions of both conditions are videotaped, with the exception of children and families in the TAU condition who take part in group-based therapy (due to data confidentiality restrictions on children and families who are not part of the study). See the trial Standard Protocol Items: Recommendations for Interventional Trials (SPIRIT) Checklist for details (in Additional file 1).

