#### Treatment permitted and not permitted during the trial

Children and families in the MATCH condition will receive the MATCH treatment only. The sole exception is that the children may receive a medication regimen deemed necessary by the clinician. Medication use is registered and tracked throughout the treatment period for all participants. No restrictions are imposed on what is offered to the children and families in the TAU condition. There are also no restrictions for participants in either condition regarding prior treatment or prior participation in any EBTs.

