#### Treatment period

There is not a set number of sessions; the MATCH therapist follows the flowchart for the primary protocol. The therapist moves on to a new module when the content of the module in question has been properly covered or when the clinical concern addressed by the module has resolved. If there is interference that prohibits the therapist from following the prescribed sequence, the therapist can use modules from a different protocol until the interference is resolved. Treatment will end when the PATH data show reasonable progress, combined with the clinical judgment that most of the improvement that is likely to happen, has been achieved. As in all treatments, some cases will not have the expected progress, and the therapist will discuss with the consultant whether another approach would be appropriate. In an article reporting on the effects of MATCH in the US, the average number of therapy sessions was 30.02 and because most sessions are conducted weekly, the average time period for treatment was about 7.5 months [23]. There are no accurate statistics available indicating what the average time in therapy is for TAU in Norway. One of the goals of this study is, however, to compare time in treatment between the two conditions.

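### Whether MATCH works is to be judged only in families who went through treatment, a set formed after randomisation and possibly selected differently in the two arms; ITT should decide both questions

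*Protocol article*

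**What the plan says.** In the protocol article, the section *The selection of participants to be included in the analyses* pairs the question of whether MATCH works with a per-protocol set: "we will employ a per-protocol design; thus only those children and families who have gone through treatment will be included". The second question, whether MATCH makes a difference in existing clinics, is paired with ITT, "in which all families randomized will be included in the analyses, regardless of whether they entered or completed treatment". The section closes: "Thus, we will analyze data using both ITT and per-protocol designs in an effort to answer these two overall questions". It does not say which analysis prevails if they disagree.

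Four statements elsewhere bear on who ends up in the per-protocol set.

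- *Treatment period*: "There is not a set number of sessions; the MATCH therapist follows the flowchart for the primary protocol".
- *Treatment period*: "Treatment will end when the PATH data show reasonable progress, combined with the clinical judgment" that most of the likely improvement has been reached. It adds that "some cases will not have the expected progress, and the therapist will discuss with the consultant whether another approach would be appropriate".
- *Intervention/Route of administration*: "Families in both conditions complete PATH, but only MATCH therapists will have access" to the responses.
- *Treatment permitted and not permitted during the trial*: "Children and families in the MATCH condition will receive the MATCH treatment only", with medication as the one exception. TAU carries no restriction.

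The PATH scores (TPA and BFS) are also listed under *Primary outcomes*.

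**The concern.** Randomisation makes the two arms comparable as randomised. Restricting both arms to families who went through treatment keeps that comparability only if the restriction removes the same kind of family from each. Three features of this trial give reason to doubt that.

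1. In MATCH, the decision to end treatment uses progress scores that are themselves primary outcomes. TAU therapists do not have those scores.
2. A MATCH child without the expected progress may be considered for another approach. Because MATCH families are to receive MATCH only, such a child may fall out of the per-protocol set. A TAU child who changes treatment is still receiving TAU and need not fall out.
3. With no set number of sessions, the article offers no exposure-based meaning of completion that would apply equally to both arms.

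At stake is the answer to the first of the two stated questions. As planned, it would rest on a comparison that randomisation no longer protects, and a difference could appear without any treatment effect. With no ranking, discordant ITT and per-protocol results could each be presented as the trial's answer.

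**Working it through.** **The plan's own figures.** The article gives no completion rate and no link between completion and outcome, so it has no figure for this bias to reproduce. From *Sample size* come 280 families, an effect size of 0.3, power .80 and alpha .05; from *Design and power*, a 50% chance of either arm, hence 140 per arm. With SD 1, n per arm = 2(z_α + z_β)²/0.3². A one-sided test needs 138 per arm (276 in total, close to 280); a two-sided test needs 175 per arm (350). Sidedness is not stated and is a separate matter. Here 0.3 serves only as a yardstick.

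**Assumptions, none from the article.** True effect zero; outcome is improvement in SD units; two-sided 5% test; SD of completers kept at 1; no adjustment for covariates or clustering. In each arm a fraction q does not complete. Non-completers are the lowest q on an index that correlates r with improvement.

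**Formulas.**

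- Shift in the completers' mean: s(q, r) = r × φ(z_q)/(1 − q), where z_q = Φ⁻¹(q).
- Spurious d = s in MATCH − s in TAU.
- SE = √(1/n_M + 1/n_T), with n = 140(1 − q) in each arm.
- False-positive rate = P(Z > 1.96 − d/SE) + P(Z < −1.96 − d/SE).

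**One case in full.** With q = 0.2 in both arms, r = 0.3 in MATCH and r = 0 in TAU:

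- φ(z_0.2) = 0.27996, so d = 0.3 × 0.27996/0.8 = 0.10499.
- n = 112 per arm, so SE = √(2/112) = 0.1336 and d/SE = 0.786.
- False-positive rate = 0.123.

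**Results** (positive d favours MATCH).

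| MATCH: q, r | TAU: q, r | Spurious d | False-positive rate |
|---|---|---|---|
| 10%, 0.3 | 10%, 0 | +0.06 | 7.5% |
| 20%, 0.3 | 20%, 0 | +0.10 | 12.3% |
| 20%, 0.5 | 20%, 0 | +0.17 | 25.8% |
| 30%, 0.3 | 30%, 0 | +0.15 | 18.1% |
| 30%, 0.5 | 30%, 0 | +0.25 | 41.2% |
| 20%, 0.5 | 20%, 0.5 | 0.00 | 5.0% |
| 20%, 0.3 | 20%, 0.5 | −0.07 | 8.2% |
| 20%, 0.3 | 40%, 0.3 | −0.09 | 9.4% |
| 20%, −0.3 | 20%, 0 | −0.10 | 12.3% |

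The first five rows put all the selection in MATCH. The sixth selects equally in both arms. The next two have stronger selection or heavier loss in TAU. The last has early improvers leaving MATCH before completion.

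Against the planning effect of 0.3, the MATCH-only rows at 20–30% loss run from about one third (0.105/0.3 = 35%) to about four fifths (0.248/0.3 = 83%).

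**Estimating an effect among the treated.** A complier-average causal effect is the ITT effect divided by the between-arm difference in receipt. If receipt meant a minimum number of sessions of any kind, and 80% met it in each arm, the denominator would be 0.80 − 0.80 = 0 and the estimate undefined. If receipt means receiving MATCH, with 80% in the MATCH arm and none in TAU, the denominator is 0.80. The estimate is then zero whenever the ITT effect is zero.

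**The case against.** The best defence is that ITT on all randomised families is already planned. The article calls this an effectiveness trial, its first aim is effectiveness, and the ITT question fits that aim. Post-assessment is to be carried out even when a clinic terminates a MATCH treatment, so the plan intends to have data for ITT. All of this stands. It makes the point one of ranking and of which set answers which question, not of a missing analysis.

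Four stronger readings are tempting, and the article does not support them.

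- *The completer result is the headline.* Both analyses are planned and neither is ranked.
- *Completing MATCH means having shown progress.* The ending rule says when treatment stops, not who counts as having gone through it. It also includes a clinical judgement that further gain is unlikely, which is partly a plateau criterion. Slow responders may simply stay longer, and the article does not say that cases without expected progress leave the set.
- *TAU ends without regard to improvement.* TAU therapists lack PATH, but the article does not describe how TAU ends. They may well judge progress in other ways.
- *The result is biased toward MATCH.* The direction depends on how selection differs between arms, and the table shows plausible patterns with zero or negative bias.

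It is also fair to say that an article may leave the exact per-protocol definition to the full protocol or analysis plan. Its absence here is not the complaint. The complaint is that the article itself fixes a post-randomisation set as the answer to one of its two questions.

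**Conclusion.** The point holds in a limited form. The question of whether MATCH works is assigned to a set formed after randomisation, ITT is tied only to the other question, and nothing says which decides. Progress data seen in one arm only, and treatment restrictions that differ by arm, make unequal selection of completers a real possibility.

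The bias cannot be sized or signed from the article. A bias toward MATCH is plausible, and at the assumed 20–30% loss with MATCH-only correlations of 0.3–0.5 it would be large enough to matter against a planning effect of 0.3. Both the loss and the absence of outcome-related selection in TAU are assumptions, so the 12–41% false-positive range illustrates one direction and is not an estimate. An analysis whose bias cannot be bounded should not be the sole answer to an efficacy question. The point is worth correcting but does not undermine the trial, because the analysis that should decide is already in the plan.

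**What to change.** - State that ITT on all randomised families is the primary, deciding analysis for both questions.
- Keep per-protocol only as a labelled sensitivity analysis. Define going through treatment by the same rule in both arms and independently of outcome, before any outcome data by arm are seen.
- If an estimate among the treated is wanted, use a complier-average causal effect with randomisation as instrument and receipt defined as receipt of MATCH itself, not as a session count common to both arms. State the assumptions, above all that assignment to MATCH has no effect on families counted as not receiving it. Partial exposure strains this if receipt is set at a high threshold.

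The cost is a few sentences of analysis wording and, if chosen, one further model. No change to recruitment, treatment or assessments is needed. The downside for the investigators is that the completer result can no longer stand alone as the answer to whether MATCH works.

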### Monitoring and safety

#### Procedures for recording of adverse events

The clinics follow internal procedures for detecting adverse events. The clinics continuously assess the proper and secure treatment of patients and their families, as they would normally do. The clinics will inform the NCCBD if any adverse events occur.

#### The type and duration of the follow-up of participants after adverse events

The clinics follow internal procedures for following up families in the case of adverse events.

#### Data Monitoring Committee (DMC)

This study is an effectiveness trial, conducted in existing child and youth mental health clinics, not in a research facility. The intervention is psychotherapeutic and is considered low risk and no more intrusive than what is being delivered to children and families in the clinics as part of their regular treatment delivery. The participating clinics have internal procedures for detecting, reporting, and following up on any adverse events in their patients. The study does not pose any restrictions on the clinics’ internal procedures for handling adverse events or from offering another treatment if deemed appropriate. In the event of the clinic terminating a MATCH treatment, the research team at the NCCBD will be informed, and post-assessment will be conducted. The trial is not blinded, as the therapists know what kind of treatment they offer the children and their families. MATCH therapists are routinely guided by US consultants with follow-up assistance from Norwegian co-consultants throughout the treatment. Interim analyses will not be conducted, in order not to bias the progression of the study.

Carandang et al. [5] reported on a set of issues to consider for mental health researchers when deciding whether to appoint a DMC for a mental health study. These issues included (1) risk of the psychiatric disorders (e.g., suicidal risk), (2) features of treatment (whether it is pharmacological), (3) research environment (extend of experience), (4) lack of information on the study population (e.g., comorbidity), and (5) lack of information about the treatment (e.g., novel and without prior results). The study population in the current study can certainly be considered vulnerable; however, information about suicide attempts (and suicidal ideation) and psychosis are collected and excluded from participation, the intervention is psychotherapeutic and is considered low risk, and the research environment consists of experienced researchers who have conducted several randomized trials with similar populations of children and youth. The researchers and the treating therapist(s) know a great deal about the children and their family. The intervention consists of known and well-tested treatment components, and it has been implemented in other settings with promising results. For these reasons, the current study has not appointed a DMC.

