### Measures

Questionnaires and interviews are administered to the families in six waves, in addition to the weekly PATH questionnaire which is filled out by children (above the age of 8 years), parents and MATCH therapists between each session throughout the course of treatment. Therapists, supervisors, and team-leaders at each clinic also fill out questionnaires. See Fig. 1 and the description of measures for details. The pre-assessement (T1) is administered after receipt of consent and prior to randomization. At 3 and 6 months (T2 and T3, respectively) into treatment, a short assessment is administered to children and parents, and these are both time-invariant and thus occur at the same time for all families enrolled, regardless of group assignment or treatment progress. Shortly after treatment has concluded, families fill out the post-assessment (T4). The time at which the post-assessment is administered varies among families depending on how long the treatment period has lasted, and so this assessment is time-varying. At 15 months (T5) after treatment initiation, another short assessment is administered. The last assessment (T6), the follow-up, is administered 1 year after the end of treatment, and so is time-variant relating to T1 (because it depends on how long treatment lasted), but is time-invariant in relation to T4 (because it is carried out 1 year post treatment conclusion)

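### The end of treatment may be counted differently in the two arms, which can make time in therapy look shorter under MATCH

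*Protocol article*

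**What the plan says.** The protocol article lists time in therapy as a primary outcome (Primary outcomes). Under Treatment period it makes the comparison an aim: "One of the goals of this study is, however, to compare time in treatment between the two conditions".

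**MATCH arm.** The section Data Monitoring Committee (DMC) says that the study does not keep clinics from following their own adverse-event procedures "or from offering another treatment if deemed appropriate". The next sentence reads: "In the event of the clinic terminating a MATCH treatment, the research team at the NCCBD will be informed, and post-assessment will be conducted". Treatment period gives a planned end rule for MATCH, based on PATH progress and clinical judgement. It also foresees cases without the expected progress, for whom "the therapist will discuss with the consultant whether another approach would be appropriate".

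**Treatment content by arm.** Under Treatment permitted and not permitted during the trial: "Children and families in the MATCH condition will receive the MATCH treatment only", with medication as the sole exception. For the other arm: "No restrictions are imposed on what is offered to the children and families in the TAU condition". Intervention/Route of administration adds: "The content and structure of TAU vary among clinics and among individual therapists". No end-of-treatment rule is given for usual care (TAU).

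**Both arms.** The Measures section words the post-assessment rule without regard to arm: "Shortly after treatment has concluded, families fill out the post-assessment (T4"). The follow-up assessment (T6) is dated one year from the end of treatment. The assessments at 3, 6 and 15 months (T2, T3, T5) follow the calendar.

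**The concern.** The article names what ends treatment in one arm and not in the other, and the two arms are defined by different kinds of content. MATCH is a specific programme that a child can leave while still attending the clinic. TAU is whatever the clinic delivers, so a child can move from one approach to another and remain in it. On the natural reading, leaving MATCH for other care triggers the post-assessment, whereas a change of approach within TAU triggers nothing.

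Two results are exposed. First, time in therapy could omit the later clinic care of children who leave MATCH while including comparable care in TAU. Those children are likely to be the ones doing poorly, so the omission would read as efficiency. Second, T6 takes its date from the end of treatment. For a child who leaves MATCH, the year before T6 can contain active clinic treatment.

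The article's own background shows that these are separate quantities. Its account of the trial against community implemented treatment reports less time in treatment and less use of additional services as two distinct findings.

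**Working it through.** No figure in the plan is at stake, so the first step is to set the text side by side.

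| Question | MATCH | TAU |
|---|---|---|
| What counts as the assigned treatment? | MATCH only, medication excepted | Anything the clinic offers |
| Planned end rule? | Yes (Treatment period) | None stated |
| Post-assessment on early termination? | Yes (DMC section) | None stated |
| Status after a move to other clinic care? | Has left the assigned treatment | Still in TAU (inferred) |
| When does time in therapy stop? | Not stated | Not stated |

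The first three rows are documented. The fourth follows from the first. The fifth is why the conclusion is that the count *may* differ, not that it does.

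**Illustration of size.** Inputs:
- From the document: 280 children with a 50% chance of each arm, so about 140 per arm; alpha .05, taken as two-sided.
- Assumed, because the document gives none: share of MATCH children who leave for other clinic care, f = 5% to 20%; uncounted later care, k = 2 to 6 months; SD of time in therapy, 3 to 5 months; equal true total care in both arms.
- For scale, Treatment period cites a mean of about 7.5 months in a US study, without an SD.

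Formulas:
- Spurious shortening in MATCH = f × k months.
- Standardised difference d = f × k / SD.
- Chance of a significant result favouring MATCH ≈ Φ(d × √(140/2) − 1.96). With d = 0 this is 2.5%.

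Middle case: 0.10 × 4 = 0.4 months; 0.4 / 4 = 0.10; 0.10 × 8.367 − 1.96 = −1.12; Φ = 0.13.

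| f | k (months) | SD (months) | Shortening (months) | d | Chance favouring MATCH |
|---|---|---|---|---|---|
| 5% | 2 | 5 | 0.1 | 0.02 | 4% |
| 10% | 4 | 4 | 0.4 | 0.10 | 13% |
| 10% | 6 | 4 | 0.6 | 0.15 | 24% |
| 20% | 4 | 4 | 0.8 | 0.20 | 39% |
| 20% | 6 | 4 | 1.2 | 0.30 | 71% |
| 20% | 6 | 3 | 1.2 | 0.40 | 92% |

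The first and last rows are the extremes of the assumed range. The effect is negligible if few children leave MATCH and serious if many do.

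**The case against.** The strongest reply is that the TAU half is not in the text. No section says that TAU time continues through a change of approach, or that time in therapy stops when MATCH is terminated. The Measures section words the post-assessment alike for all families, and the individual stopping rules cover both MATCH and regular practice. The termination sentence itself sits in an argument for not appointing a monitoring committee and reads as a notification rule. All of this stands, and it rules out saying that the arms are known to be measured differently. It does not remove the asymmetry: *concluded* is left undefined, and the stopping rules concern safety, viability, custody and consent, not a change after poor response.

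Many changes of direction also stay inside MATCH. Modules can be borrowed across protocols and a new protocol started, and the other approach discussed with the consultant need not lie outside MATCH. This stands too: only true exits from MATCH matter, and their number is unknown.

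A reader might infer that T6 in TAU always follows the end of all care. Nothing supports that, since TAU families may return to care within the year. Service use and medication are asked about at T1, T4 and T6 in both arms, so later care can be partly described.

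A reader might also set an assumed bias of 0.15 to 0.30 beside the effect of 0.3 in the sample-size section. That 0.3 belongs to the main-effect analysis, described for the pre-, post- and follow-up assessments and not for time in therapy, and the bias range is wholly assumed.

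Finally, an operational definition of time in therapy is commonly left to an analysis plan. Its absence is not the point here. The point is that the text fixes a data-collection event for one arm only, and an analysis plan cannot use a closing date that nobody collected.

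**Conclusion.** The concern holds in limited form. The article attaches the post-assessment to termination of MATCH, allows other clinic treatment afterwards, gives an end rule for MATCH only, and defines TAU so broadly that a change of approach remains TAU. The end of treatment may therefore be counted differently by arm. Any resulting error in time in therapy would favour MATCH, and the MATCH follow-up year before T6 may include active clinic care.

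The size cannot be determined from the document. Under the stated assumptions the spurious difference runs from 0.1 to 1.2 months (d about 0.02 to 0.40), with a middle case of 0.4 months (d 0.10), where a false finding in favour of MATCH has a 13% chance instead of 2.5%. Intention-to-treat analysis keeps every randomised family but does not change when treatment is deemed to end. T2, T3 and T5 are free of the problem.

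**What to change.** This is a change to measurement only and leaves clinical care as it is.

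1. For the between-arm comparison, count time in therapy in both arms to one event: the date the clinic closes all treatment for the referred problem, whatever its content. Use the same start event in both arms.
2. Record the date MATCH stopped as a separate variable, and report time on MATCH descriptively.
3. Keep the post-assessment as now triggered. Taking it when a child leaves MATCH is defensible, because waiting until all care ends would mix other treatment into the MATCH post-score. Flag MATCH families who go on to other clinic care, so that their T4 and T6 results can be read accordingly.
4. Use the parent CBCL internalizing and externalizing scales at 3, 6 and 15 months, already planned for mixed-effects analysis, as the symptom comparison free of this problem.

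**Cost.** Clinics must report one further closing date for families who leave MATCH for other care. Recruitment began in March 2016, so for earlier families the date would have to be requested in retrospect. The existing clinician end-of-treatment questionnaire and the service-use questions give a place to collect it. The MATCH figure for time in therapy may become less favourable.
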